### Organization framework

The coordination of the NASCITA study will be provided by the team of the Laboratory for Mother and Child Health of the Mario Negri Research Institute that integrates different expertise and competence with a long-standing experience in multicenter clinical research. The coordinating center will also carry out data collection, storage, management, and analysis. An independent scientific committee consisting of representatives of different disciplines and realities (including lay people) will monitor the development and results of the project. A network of local contacts (contact person per area) between pediatricians has been set up so that each node, representative of a setting, will act as a bridge to the coordinating center in conducting the study. An additional group of individual pediatricians has been identified to act as specialists in their area of expertise, e.g., environment, nutrition, and neurodevelopment.

### Materials produced

A specific web portal for the NASCITA cohort study was developed (https://coortenascita.marionegri.it) to collect data, through a web-based form, and to provide findings and other information during the study period, also with the use of graphics on the analyses and data collected based on a successful approach already reported by the coordinating center [19, 35]. The NASCITA project will use ad-hoc information material, the study website, and newsletters to keep in touch with study participants. Health promotion measures within the cohort will be implemented through the use of these tools, and will also be made available to the general population through publications on the website.

### Ethics and dissemination

The study was approved by the Fondazione IRCCS Istituto Neurologico Carlo Besta’s Ethics Committee (6 February 2019, Verbale n.59). A consent form for participation will be signed by the pediatricians upon their first access to the web site. A paper consent form will be signed by parents at the first visit. This form includes the consent to data collection at each contact with the pediatrician during the six-year study period (first 6 years of the child’s life). The filled in consent form will be stored by the pediatrician for ten years. Withdrawal from the study is guaranteed at any time both to pediatricians and parents. When consent is withdrawn, the child’s data collected up to that point will be kept in the analyses, but no further data will be collected. Standard procedures for the protection of confidential individual information will be applied according to national and international ethical recommendations and guidelines as well as national legal regulations. Data will be pseudonymized and all analyses will be conducted with fully anonymized data sets.

A newsletter report will periodically be sent to the pediatricians and uploaded on the web site. During the study, different tools will be used to update the participating families. Ad-hoc information material will be created and will be disseminated to families through newsletters and the website. Collected data will be periodically analyzed according to the aims of the project, and findings reported to lay people and the scientific community.

The coordinating center will provide the information, but the pediatricians will also be able to provide the families with information deriving from the cohort during their visits.When the enrolled children reach the age of 6 years, if not decided otherwise in the meantime, their personal files will no longer updated, but will be kept for another 10 years in the database.

NASCITA proposes to be a resource for the research community, so data will be available to public researchers outside the NASCITA research group upon request for collaborative research initiatives, after approval by the scientific committee.

## Discussion

### Application of study results

The information gathered by the NASCITA birth cohort study will be valuable for child health care and public health policy making. Information concerning the children will be collected at specific ages that coincide with routine contact moments, so findings from NASCITA that can be translated into parental advice or other preventive measures can directly be incorporated into routine protocols and reach a large group of children and their parents at once. Furthermore, study results on (modifiable) risk factors, disease prognosis, and medication use may also be relevant for family pediatricians.

Moreover, NASCITA findings may aid policy and decision makers, who need scientific evidence to develop and implement prevention and intervention strategies. NASCITA will progressively build on a database containing policy relevant information on a broad range of determinants and health outcomes that may be beneficial in responding to certain public health issues. NASCITA results may also contribute to the evidence towards the need to build up a permanent national observatory on child health and development.

### Strengths and limitations of this study

NASCITA is entirely embedded in the child health care practice foreseen by the National Health Service and provided by family pediatricians. Recruitment and follow-up coincide with routine contact moments, so broad participation and follow-up rates are expected. Collaboration with other cohorts is foreseen. The NASCITA cohort data will be linkable and integrable with other data sources, such as routinely collected health data or data from other projects, as part of scientific collaborations.

High participation rates would allow an appropriate description and evaluation of all the different national territorial clusters. Moreover, NASCITA will provide opportunities to initiate new, experimental studies in subgroups of the cohort, and will contribute relevant information on determinants and health outcomes to policy and decision makers.

Since loss to follow-up is always a cause for concern in cohort studies and should be minimized, efforts have been made to establish a close and trust-based relationship with all participants. These efforts involve the creation of ad-hoc information material, the website, and newsletters to keep in touch with the study participants and to apply health promotion measures within the cohort. The estimated 20% loss to follow-up would, in any case, lead to a sample size that is large enough to be able to study common childhood exposures and outcomes. With the parents’ consent, data on children withdrawing after 12 months of age will be considered in the analysis.

A limit of the NASCITA study (as with any observational study) is the possibility of selection bias in the study population. The pediatricians recruited represent a co-operative sample, not a random sample, and should not be considered to be representative of the population of family pediatricians. The pediatricians, for example, could be more sensitive to better care practices or recommendations, and could influence the parents accordingly, promoting, for example, reading out loud to children. The target population of the study, however, will be the newborns (and their families) who are assigned to the pediatricians by the LHU based on places that have been freed up with those pediatricians. No selection bias in the population should therefore occur.

The rising number of migrant patients means increasing potential language barriers in the communication between a healthcare practitioner and a patient who speaks a different language, and miscommunication may occur in healthcare settings [4]. Although this is a situation that family pediatricians have to face daily, some foreign language speaking parents, in particular recent immigrants, may decide not to participate in the study and this may create a minimal selection bias.

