## Methods

### Study area and setting

Italy is located in southern Europe and comprises the long, boot-shaped Italian peninsula, the southern side of Alps, the large plain of the Po Valley and some islands including Sicily and Sardinia. Almost 40% of the Italian territory is mountainous, and there is a coastline of 7600 km on the Adriatic Sea, Ionian Sea, Tyrrhenian Sea, Ligurian Sea, Sea of Sardinia and Strait of Sicily. Italy is subdivided into 20 regions and is further divided into 14 metropolitan cities and 96 provinces, which in turn are subdivided into 7960 municipalities. A gaping North–South divide is a major factor of socio-economic weakness and can be noted by the huge difference in statistical income between the northern and southern regions and municipalities [17]. Twenty-two geographic clusters were identified as representative of the country based on geographic and socio-economic characteristics and administrative divisions, using the National Statistics Institute definitions for each town/city [18]. See Fig. 1 for the geographical distribution of the NASCITA cohort. Pediatricians and newborns of all the 22 identified clusters will be involved in the study.

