### Recruitment

NASCITA will be embedded in Italian pediatric primary care practice. The coordination center has collaborated over the years with a network of hundreds of family pediatricians, as documented by numerous collaborative publications [19–22], which represents the first interlocutor to whom we proposed participation in the study. The basis of this network is the national Pediatric Cultural Association (ACP), with around 2000 members consisting mainly of family pediatricians. In order to have as large a sample as possible we therefore used the already existing network to begin the first identification of the locally representative pediatricians, who were then asked to identify additional pediatricians, not necessarily belonging to the ACP, in their areas for participation. Other pediatric scientific societies and associations will be contacted to expand collaboration and the number of participating pediatricians. In this regard, detailed information concerning the study will be disseminated through national pediatric journals and internet-based resources to increase recruitment. Recruitment will be based on the voluntary participation of interested pediatricians who can guarantee seven years of professional activity so that they can follow the enrolled newborns for the whole study period. This approach to enrolling pediatricians can be defined as a mixed method using also non-probability sampling techniques (convenience and purposive sampling) applied to choose a sample of subjects/units from a population [23, 24]. In terms of the work effort requested of the pediatricians, case report forms were discussed with a group of family pediatricians and tested by them in a pilot phase. The time needed to fill the forms was recorded by each participant and difficulties or doubts were reported to the coordinating center. The participants in the pilot phase assured the coordinating team that the data collection was feasible.

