### Analysis plan

The analysis plan for the NASCITA cohort entails the investigation of several exposures and outcomes in order to address numerous research questions.

The main independent variables that will be tested are:

Maternal/paternal age.

Education level.

Employment.

Marital status.

Parental health status.

Parental lifestyle habits (smoking, alcohol).

A few examples of the dependent variables are:

Vaccination in pregnancy.

Folic acid prophylaxis.

Birthweight.

Duration of breastfeeding.

Reading out loud.

Sleep position.

Overweight and obesity.

Neurocognitive development.

Prescription prevalence and appropriateness.

Nursery school attendance.

A few of these variables will be tested as both independent and dependent variables based on the kind of analyses (e.g., reading out loud will be the dependent variable while testing the influence of maternal age or educational level, but will be considered an independent variable when possible factors influencing children’s development are tested).

Examples of the NASCITA STUDY’S research questions are:

- the relationship between mothers’ age, education level, and geographic area (independent variables) and vaccination in pregnancy (Influenza and Tdap vaccines) (dependent variable);

- the association between maternal smoking in pregnancy (independent variable) and birthweight (dependent variable);

- the relationship between pregnancy, perinatal, and newborn growth characteristics and occurrence of adverse outcomes (i.e., obesity, hypertension, wheezing, eczema, hay fever, and asthma);

- the relationship between parents’ educational level (independent variable) and duration of breastfeeding (at discharge from hospital and at 3 and 6 months) (dependent variable);

- the relationship between parents’ educational level (independent variable) and children’s weight and BMI/percentage of overweight/obese status (dependent variable);

- the association between lifestyle factors and health inequalities and the trajectory of health in the preschool period;

- the association between geographical setting and nursery school attendance;

- the association between geographical setting and quality of care in terms of prevalence and appropriateness of drug prescriptions.

In all of the of the analyses, the effect of the geographic and environmental setting will be evaluated.

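### Assignment of newborns by the local health unit does not support the statement that no selection bias should occur

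*Protocol article*

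**What the plan says.** All references are to the protocol article.

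- **Strengths and limitations of this study.** The paragraph on selection opens by saying that a limit of the study "is the possibility of selection bias in the study population". It describes the pediatricians as a co-operative, non-random sample who "should not be considered to be representative of the population of family pediatricians", and adds that they "could be more sensitive to better care practices or recommendations, and could influence the parents accordingly". It then names as the target population the newborns and families assigned to those pediatricians by the local health unit, and concludes: "No selection bias in the population should therefore occur".
- **Same section, next paragraph.** Some foreign-language parents "may decide not to participate in the study and this may create a minimal selection bias". No figure is given.
- **Recruitment.** Pediatricians join voluntarily, starting from an association network and extended through local contacts and other societies, and must be able to guarantee seven years of activity. The article calls this a "mixed method using also non-probability sampling techniques (convenience and purposive sampling").
- **Inclusion and exclusion criteria.** Children whose parents do not agree to take part are excluded.
- **Study area and setting.** "Twenty-two geographic clusters were identified as representative of the country".
- **Background** and **Application of study results.** The overall aim concerns the health of Italian children, and the results are meant to serve policy makers and possibly a permanent national observatory.
- **Aims** and **Analysis plan.** Care by family pediatricians is compared between areas. One listed question is "the association between geographical setting and quality of care in terms of prevalence and appropriateness of drug prescriptions".

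**The concern.** A child enters the cohort only if three things happen: the practice joins, the child is assigned to that practice, and the parents consent. The article's argument covers the second step alone, yet its conclusion is worded for the whole population.

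Two uses of the data are exposed. The first is a pooled prevalence offered as a figure for Italian children, which would reflect the mix of areas, practices and families that took part. The second is any comparison of care or prescribing between areas, where the provider of the care is the unit that the article itself calls non-representative. A difference between areas could then be a difference in who volunteered. The article also gives the route by which volunteering reaches family outcomes: it says that participating pediatricians may promote reading aloud, and reading aloud is a listed dependent variable.

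**Working it through.** **1. The passages side by side**

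| Step into the cohort | What the article says | Does assignment by the local health unit act on it? |
|---|---|---|
| Practice joins | Voluntary, network-based, convenience and purposive, seven-year guarantee | No |
| Newborn reaches a participating practice | Assigned according to places freed up | Yes, it limits selection of families within the practice |
| Parents consent | Refusers excluded; some foreign-language parents may refuse | No |

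Only the middle row supports the conclusion. If the target population is narrowed to newborns assigned to participating pediatricians, the first row drops out but the third remains.

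**2. The plan's own figures**

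- Newborns per pediatrician: 450,000 / 7500 = 60, as stated.
- Minimum cohort as a share of births: 5000 / 450,000 = 1.1%, stated as about 1%.
- Retained after 20% loss: 5000 × 0.80 = 4000, as stated.

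From these, assuming a one-year intake with full consent, 5000 newborns need 5000 / 60 = 83 pediatricians. That is 83 / 7500 = 1.1% of family pediatricians and, on average, 83.3 / 22 = 3.8 per cluster. A comparison of prescribing between clusters would rest on about four volunteers in each.

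**3. Illustration of size (all shifts assumed; the documents give none)**

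The outcome is exclusive breastfeeding until 6 months, 42.7% in Table 1. I take n = 5000, because the section on study population size expects negligible attrition in the first two years.

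- SE = sqrt(0.427 × 0.573 / 5000) = 0.70 points; 95% half-width = 1.96 × 0.70 = 1.37 points.
- Coverage under bias b = Φ(1.96 − b/SE) − Φ(−1.96 − b/SE):

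| Assumed bias b (points) | Coverage of the nominal 95% interval |
|---|---|
| 1 | 70% |
| 2 | 18% |
| 5 | about 0% |

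With n = 4000 (SE 0.78 points), a 1-point bias gives 75%. This SE treats children as independent. Clustering within practices would widen a correctly computed interval, so the loss of coverage would be smaller than shown.

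How such shifts could arise:

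- *Practices.* Bias = (1 − sampled share) × difference between participating and other practices. With a share of 1.1% and assumed differences of 2, 5 or 10 points, the bias is 2.0, 4.9 or 9.9 points.
- *Area mix.* If one macro-area supplied 60% of the cohort but 45% of births, and the outcome differed by 10 points (all assumed), the shift is (0.60 − 0.45) × 10 = 1.5 points.
- *Refusal.* Let a group have share m and refusal r, and let its outcome differ by d. Its observed share is m(1 − r) / [m(1 − r) + 1 − m], and the bias is d times the fall in share. With d = 20 points: m = 10%, r = 20% gives 20 × (0.100 − 0.082) = 0.4 points; m = 20%, r = 50% gives 20 × (0.200 − 0.111) = 1.8 points. All values are assumed.

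**The case against.** The article can be defended on several points, and some of the defence stands.

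- **The wording is soft and scoped.** It says bias *should* not occur, and it says so of newborns assigned to participating pediatricians. A reader might infer a claim that bias cannot occur; the text does not go that far. But even for the narrower population, refusal is still open, and that population is not the national one used elsewhere in the article.
- **The pediatricians are openly described as non-representative.** A reader might infer that the article offers its care results as those of Italian pediatricians in general. It does not; it warns against this. What remains is that the aims and the analysis plan set out area comparisons of care without that warning.
- **Weighting is not excluded.** A reader might infer that the study is committed to unweighted prevalences. The analysis plan says only that categorical variables are summarized as proportions and that multivariate analyses will follow. A condensed article may leave weighting to a fuller plan, so its absence here is not a defect.
- **There is mitigating text.** Recruitment reaches beyond the association, all 22 clusters are to be involved, and the effect of geographic setting is to be evaluated in every analysis. Most listed questions are associations, and the word representative is applied to the clusters, not to the enrolled children. This lowers the stakes for many analyses. It does not correct a pooled national prevalence or a comparison of volunteers between areas.

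**Conclusion.** The concern holds as a fault in what the article states. The sentence does not follow from the reason given, and it conflicts with the opening of its own paragraph, with the recruitment and consent rules, and with the admission about foreign-language parents. This rests on the text alone and needs no assumption.

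The size is unknown. The coverage figures show only that small shifts matter at this sample size: a bias of 1 to 2 points is comparable to the simple half-width of 1.37 points, and enrolling more children would narrow the interval without removing the bias. A reader might take these figures as evidence that the cohort is biased by that much. The documents do not support this, because every shift is assumed.

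**What to change.** 1. **Replace the sentence.** State that assignment by the local health unit limits selection of families only within participating practices, and that selection can still act through pediatrician volunteering (including the seven-year condition) and parental refusal. Reconcile this with the description of the clusters as representative, with the recruitment section, and with the paragraph on foreign-language parents, where the bias is called minimal without a figure. Cost: a text change.
2. **Carry the caveat forward.** In the aims and the analysis plan, word the area comparisons of care and prescribing as applying to participating pediatricians. Cost: a text change.
3. **Where a pooled prevalence is presented as national,** report it post-stratified to births per area and to the national birth margins cited for Table 1 (for example gestational age, multiple birth, assisted procreation), alongside the crude figure. State that this corrects area and family mix only and cannot remove the effect of volunteer pediatricians on care or parental behaviour. Cost: national births by area must be obtained, one analysis step is added, and the weights inflate the variance somewhat.

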## Data Availability

Not applicable.

## Abbreviations

CRF: Case Report Form
eCRF: Electronic Case Report Form
LHU: Local Health Unit
NASCITA: *NAscere e creSCere in ITAlia*
